### Hantering av studiepreparat:

- När Formulaid-förpackning tinas upp och öppnas fylls 1ml sprutor (för enteral användning) med 1ml Formulaid olja. Sprutorna förvaras i kylskåp tills användning.
- Formulaid dosen ges en gång om dagen oblandad i matsond /oralt före måltid. Sonden spolats genom den efterföljande måltiden med bröstmjolk eller modersmjölksersättning. Ambitionen är att försöka ge Formulaid även om barnet fastar t.ex. p.g.a. retentioner. Ge då Formulaid innan man ger tillbaka retentionen och spola rent sonden med lite luft efteråt. Det är upp till ansvarig kliniker att avgöra om Formulaid kan administreras till det enskilda barnet.
- Under hemsjukvård (när barnen vårdas i hemmet) får föräldrar med sig förfyllda sprutor med vikthanpassad dos för en vecka eller fram tills nästa hemsjukvårdsbesök. Vikt kontrolleras minst en gång per vecka.
- Efter utskrivning fortsätter barnet att erhålla förfyllda sprutor till en ålder motsvarande 40 veckor postmenstruell ålder.
- Om patienter flyttas till något annat sjukhus (Ej studie-center) får hemmakliniken ombesörja transport av Formulaid till aktuellt sjukhus, i övrigt rutin enl ovan.

### Övrigt

- Mål för full enteral Nutrition: 150-180 ml/kg/dygn
- Multivitamin droppar (Unimedic) ska ges till samtliga barn enligt nedanstående dosering fram tills en uppnådd postmenstruell ålder 40+0 veckor och därefter enligt lokala riktlinjer.
 

|        |            |
|--------|------------|
| <2 kg  | 8 droppar  |
| 2-3 kg | 11 droppar |
| >3 kg  | 8 droppar  |
- PreNAN Discharge är den modersmjölksersättning som i första hand ska användas fram till en uppnådd postmenstruell ålder 40+0 veckor.

|                                     |  |                                    |              |
|-------------------------------------|--|------------------------------------|--------------|
| STATISTISKA KONSULTGRUPPEN          |  | Statistical Analysis Plan          |              |
| Protocol:
Mega Donna Mega |  | Protocol No:
MEGADONNAMEGA 16-7 |              |
|                                     |  | Version:
1.0                    | Page 1 of 21 |

## LIST OF ABBREVIATIONS

| Abbreviation | Definition                             |
|--------------|----------------------------------------|
| AE           | Adverse Events                         |
| AIC          | Akaike's Information Criterion         |
| ASA          | American Statistical Association       |
| BPD          | Bronchopulmonary Displasia             |
| BL           | Birth Length                           |
| BW           | Birth Weight                           |
| CI           | Confidence Interval                    |
| DBP          | Diastolic Blood Pressure               |
| DTI          | Volumetric and Diffusor Tensor Imaging |
| GA           | Gestational age                        |
| GDM          | Gestational Diabetes Mellitus          |
| HC           | Head Circumference                     |
| HR           | Hazard Ratio                           |
| IP           | Investigational Product                |
| IQR          | Interquartile Range                    |
| ITT          | Intention-To-Treat                     |
| IVH          | Cerebral Intraventricular Haemorrhage  |
| MMRM         | Mixed Models for Repeated Measures     |
| MRI          | Magnetic Resonance Imaging             |
| NEC          | Necrotizing Enterocolitis              |
| PDA          | Patent Ductus Arteriosus               |
| PMA          | Postmenstrual Age                      |
| PNA          | Postnatal Age                          |

|                                     |  |                                    |              |
|-------------------------------------|--|------------------------------------|--------------|
| STATISTISKA KONSULTGRUPPEN          |  | Statistical Analysis Plan          |              |
| Protocol:
Mega Donna Mega |  | Protocol No:
MEGADONNAMEGA 16-7 |              |
|                                     |  | Version:
1.0                    | Page 6 of 21 |

|     |                            |
|-----|----------------------------|
| PP  | Per Protocol               |
| PT  | Preferred Term             |
| ROP | Retinopathy of Prematurity |
| RR  | Relative Risk              |
| SAP | Statistical Analysis Plan  |
| SBP | Systolic Blood Pressure    |
| SD  | Standard Deviation         |
| SDS | Standard Deviation Score   |
| SOC | System Organ Class         |

|                                     |  |                                    |              |
|-------------------------------------|--|------------------------------------|--------------|
| STATISTISKA KONSULTGRUPPEN          |  | Statistical Analysis Plan          |              |
| Protocol:
Mega Donna Mega |  | Protocol No:
MEGADONNAMEGA 16-7 |              |
|                                     |  | Version:
1.0                    | Page 7 of 21 |

#### Document note:

This Statistical Analysis Plan (SAP) is describing the planned statistical analyses to be performed for the MDM study's first publication including study population description, evaluation of primary efficacy analysis, important secondary analyses and summary of adverse events.

The SAP is based on study protocol MEGADONNAMEGA 16-7, version 7b from June 2017, and the study link at <https://clinicaltrials.gov>.

The statistical analyses planned and that will be included in the first publication are applying the recently published guidelines by the American Statistical Association (ASA) that are currently employed by e.g. NEJM:

1. Ronald L. Wasserstein, Allen L. Schirm & Nicole A. Lazar (2019) Moving to a World Beyond " $p < 0.05$ ", The American Statistician, 73:sup1, 1-19, DOI:10.1080/00031305.2019.1583913
2. Ronald L. Wasserstein & Nicole A. Lazar (2016) The ASA Statement on  $p$ -Values: Context, Process, and Purpose, The American Statistician, 70:2, 129-133, DOI: 10.1080/00031305.2016.1154108
3. Alex Dmitrienko, and Ralph B. D'Agostino, Multiplicity Considerations in Clinical Trials. 2018 N Engl J Med 2018;378:2115-22.
4. David Harrington, Ralph B. D'Agostino, Constantine Gatsonis, Joseph W. Hogan, David J. Hunter, Sharon-Lise T. Normand, Jeffrey M. Drazen, and Mary Beth Hamel. New Guidelines for Statistical Reporting in the Journal. 2019 N Engl J Med 381;3

|                                     |  |                                    |              |
|-------------------------------------|--|------------------------------------|--------------|
| STATISTISKA KONSULTGRUPPEN          |  | Statistical Analysis Plan          |              |
| Protocol:
Mega Donna Mega |  | Protocol No:
MEGADONNAMEGA 16-7 |              |
|                                     |  | Version:
1.0                    | Page 8 of 21 |

## 1 STUDY DETAILS

### 1.1 Study Objectives

The primary objective in this study is to investigate whether enteral administration of AA and DHA in addition to commonly used regimens with parenteral olive based lipid emulsion (Clinoleic) compared to Clinoleic alone prevents the sight threatening disease Retinopathy of Prematurity (ROP).

The secondary objectives in this study are to evaluate following:

1. Postnatal serum fatty acid composition in preterm infants with and without AA:DHA supplementation
2. Postnatal brain development, as assessed by Magnetic Resonance Imaging (MRI), Volumetric and Diffusor Tensor Imaging (DTI) at 40 weeks postmenstrual age and motor and cognitive development at 2 years corrected age and 5.5 uncorrected age. *(data will be available and analysed at later stage)*
3. Neonatal glucose metabolism *(data will be available and analysed at later stage)*
4. Postnatal growth development (weight, length, head circumference)
5. Frequency of neonatal morbidities such as Bronchopulmonary Displasia (BPD), cerebral Intraventricular Haemorrhage (IVH), Patent Ductus Arteriosus (PDA), sepsis and Necrotizing Enterocolitis (NEC)
6. Postnatal body composition by Pea-Pod *(data will be available and analysed at later stage)*

### 1.2 Study Design

This study is a randomized intervention, multi-center study to determine the role of fatty Acids in serum and breast milk in preventing ROP. Infants without major malformations born at a gestational age (GA) of <28 weeks +0 days will be included.

Randomization will be as follows; GA  $\leq$  24 weeks +6 days, n=84, GA 25 weeks +0 days to  $\leq$  26 weeks +6 days, n=84 and GA 27 weeks +0 days to  $\leq$  27 weeks +6 days, n=42 (in order to receive equal number of infants with conventional treatment and infants treated with AA:DHA supplementation in relation to morbidity outcome. In order to adjust for center variability each center (n=3) will recruit as follows; GA  $\leq$  24 weeks +6 days, n=14 (conventional) +14 (treated), GA 25 weeks+0 days to  $\leq$  26 weeks +6 days, n=14 (conventional) +14 (treated) and GA 27 weeks +0 days to  $\leq$  27 weeks +6 days, n=7 (conventional) +7 (treated).

Study Flow Chart

|                                                                                                                                                                     | d
a
y
0 | d
a
y
1 | d
a
y
2 | ho
ur
7
2 | d
a
y
4 | d
a
y
5 | d
a
y
6 | d
a
y
7 | d
a
y
14 | W
3 | W
4 | W
5 | W
6 | W
7 | P
M
A
30+
0
+-
24h | P
M
A
31+
0
+-
24h | P
M
A
32+
0+-
24h | P
M
A
33+
0+-
24h | P
M
A
34+
0+-
24h | P
M
A
35+
0+-
24h | P
M
A
36+
0+-
24h | P
M
A
37+
0+-
24h | P
M
A
38+
0+-
24h | P
M
A
39+
0+-
24h | P
M
A
40+
0+-
24h |
|---------------------------------------------------------------------------------------------------------------------------------------------------------------------|------------------|------------------|------------------|--------------------|------------------|------------------|------------------|------------------|-------------------|--------|--------|--------|--------|--------|--------------------------------------|--------------------------------------|----------------------------------|----------------------------------|----------------------------------|----------------------------------|----------------------------------|----------------------------------|----------------------------------|----------------------------------|----------------------------------|
| Datum                                                                                                                                                               |                  |                  |                  |                    |                  |                  |                  |                  |                   |        |        |        |        |        |                                      |                                      |                                  |                                  |                                  |                                  |                                  |                                  |                                  |                                  |                                  |
| Gestational age (weeks+days)                                                                                                                                        |                  |                  |                  |                    |                  |                  |                  |                  |                   |        |        |        |        |        |                                      |                                      |                                  |                                  |                                  |                                  |                                  |                                  |                                  |                                  |                                  |
| Patient info/consent within 36 h                                                                                                                                    | x                |                  |                  |                    |                  |                  |                  |                  |                   |        |        |        |        |        |                                      |                                      |                                  |                                  |                                  |                                  |                                  |                                  |                                  |                                  |                                  |
| Physical exam                                                                                                                                                       | x                |                  |                  |                    |                  |                  |                  |                  |                   |        |        |        |        |        |                                      |                                      |                                  |                                  |                                  |                                  |                                  |                                  |                                  |                                  |                                  |
| Weight+ Length + Head circumference ± 3d from sampling                                                                                                              | x                |                  |                  |                    |                  |                  |                  | x                | x                 | x      | x      | x      | x      | x      | x                                    | x                                    | x                                | x                                | x                                | x                                | x                                | x                                | x                                | x                                | x                                |
| Registration of HR+MABP every second hour up to day 7 (excel)                                                                                                       | x                | x                | x                | x                  | x                | x                | x                | x                |                   |        |        |        |        |        |                                      |                                      |                                  |                                  |                                  |                                  |                                  |                                  |                                  |                                  |                                  |
| Study sample cord blood (2 ml). 0h, 72h, d7, d14 (+- 6 h) every other week until PMA 29w and thereafter at 30, 32, 34, 36, and 40 weeks PMA
(0,6 ml), (+- 24 h). | x                |                  |                  | X                  |                  |                  |                  | x                | x                 | x      | x      | x      | x      |        | x                                    |                                      | x                                |                                  | x                                |                                  | x                                |                                  |                                  |                                  | x                                |

|                                     |  |                                           |               |
|-------------------------------------|--|-------------------------------------------|---------------|
| STATISTISKA KONSULTGRUPPEN   |  | Statistical Analysis Plan                 |               |
| Protocol:
Mega Donna Mega |  | Protocol No:
MEGADONNAMEGA 16-7 |               |
|                                     |  | Version:
1.0                    | Page 11 of 21 |

### 1.3 Treatment Groups

A randomized intervention study of 210 infants in total, 105 in the Conventional (Clinoleic) group and 105 in the Treated (Clinoleic + AA:DHA) group.

Enteral supplementation with AA:DHA will start at second enteral feeding after birth and continue once daily to postmenstrual week 40 + 0. The supplementation will be delivered prior to feeding (0.1-1ml, according to dosing scheme, see Appendix A in the protocol). If the infant does not tolerate any enteral feeding, the supplement will be given as long as gastric retention is administered.

The intervention group will receive a daily dose of 100 mg AA/kg/day and 50 mg DHA/kg/day (Formulaid™ 2:1 DSM). Dose adjustment will be performed after the infant has regained its birthweight and weight gain results in an increase of 0.1 ml or more (see protocol Appendix A).

### 1.4 Sample Size

The sample size text below is provided in the study protocol version 7b.

The mean incidence of any ROP in an age-matched population (22 weeks + 0 days to 27 weeks + 6 days of GA at birth) in Sweden during the years 2008 – 2012 is calculated to 42%. Assuming an alpha of 5%, a power of 80% and a 50% reduction in incidence of any ROP, i.e. from 42% to 22%, a sample size of 80 subjects per treatment group is required. The reduction in any ROP with AA:DHA supplementation is based on efficacy in previous publications.

A total of 105+105 subjects will be included to compensate for protocol violations (experience gained in pilot study) and drop-outs (e.g. a perinatal death rate of approximately 15% at these gestational ages).

## 2 STUDY POPULATIONS

### 2.1 Definition of Study Populations

#### 2.1.1 Intention-To-Treat Population

All randomized subjects, being correctly included according to the inclusion/exclusion criteria, and have been treated will be included in the Intention-To-Treat (ITT) population.

The final definition of patients included in the ITT population will be made at the clean file meeting prior to database lock. Any exclusions will be described in detail in the clean file protocol.

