##### **A. Conventional parenteral fatty acid treatment with Clinoleic**

##### **B. Enteral supplement of AA (100mg/kg/day) and DHA (50 mg/kg/day) from birth to 40 weeks postmenstrual age in addition to conventional parenteral fatty acid treatment with Clinoleic.**

Enteral supplementation with AA:DHA will start at second enteral feeding after birth and continue once daily to postmenstrual week 40 + 0. The supplementation will be delivered prior to feeding (0.1-1ml, according to dosing scheme, Appendix A). If the infant does not tolerate any enteral feeding, the supplement will be given as long as gastric retention is administered.

The intervention group will receive a daily dose of 100 mg AA/kg/day and 50 mg DHA/kg/day (Formulaid™ 2:1 DSM). Dose adjustment will be performed after the infant has regained its birthweight and weight gain results in an increase of 0.1 ml or more (see Appendix A).

Formulaid™ is produced from a blend of algal, fungal, and high oleic sunflower oils, and contains AA and DHA (triglyceride form) in a ratio of 2:1. Approximate concentrations are 265 mg/g and 135 mg/g. The study oil will be dispensed 1ml purple syringes long time stored at -80 C. Syringes are then provided to the neonatal ward where they can be stored for up to three months in +4 - +8 °C. .

As we will have clinical record forms (CRF's) online the randomization is given in the CRF when the patient's parents have agreed to participate in the study.

Randomization will be as follows; GA  $\leq$  24 weeks +6 days, n= 84, GA 25 weeks +0 days to  $\leq$  26 weeks +6 days, n= 84 and GA 27 weeks +0 days to  $\leq$  27 weeks +6 days,

n=42 (in order to receive equal number of infants with conventional treatment and infants treated with AA:DHA supplementation in relation to morbidity outcome. In order to adjust for center variability each center (n=3) will recruit as follows; GA  $\leq$  24 weeks +6 days, n= 14 (conventional) +14 (treated), GA 25 weeks+0 days to  $\leq$  26 weeks +6 days, n= 14 (conventional) +14 (treated) and GA 27 weeks +0 days to  $\leq$  27 weeks +6 days, n=7 (conventional) +7 (treated).

The treating nurse/doctor will receive the randomization on-line. The examiners (ophthalmologists, radiologists and psychologists) will be blinded for fatty acid treatment regime. The duration of parenteral nutrition and the amount of fatty acids administered will be according to clinical routines.

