### Preterm Child - Conventional fatty acid supplementation

A preterm child that is randomized to conventional treatment receives Clinoleic (with Vitalipid infant and Soluvit supplementation) according to regular clinical practice and routines as described below.

For all preterm infants the parenteral nutrition with glucose, amino acids and lipids is introduced within the first 24 hours of life. The infusion of lipid emulsion (Clinoleic 20%) is gradually increased during the first days of life to a maximum of 3,5g/kg/24 h at day 3 to 5 of life. Consequently, a preterm infant with a birth weight of 1 kg will receive a maximum of 15 ml lipid emulsion/24 h (3 g/kg) which, according to Brans et al (45) is within acceptable levels (i.e 2-3 g/kg/day) for Very low birth weight (VLBW) infants. Enteral feeding with human breast milk is introduced from the first day of life. According to our clinical practice we start with 1-5 ml/kg every third hour depending of maturity and birth weight. The amount of breast milk is slowly and carefully gradually increased during the first 7 to 10 days of life until the infant is fully enteral fed. With increasing enteral amounts the parenteral dose of lipid emulsion is decreased. Some of the most immature infants may have problems to tolerate increased enteral feeding leading to a longer period of parenteral feeding in low doses.

In conclusion, feeding VLBW infants according to clinical practice and routine are a regiment with *partial* parenteral nutrition combined with enteral nutrition.

If an infant does not tolerate any enteral feeding (for example gut problems as NEC or during any kind of surgery) give Formulaid™ before giving back the retention and flush the probe with little air afterwards. It is up to the responsible clinician to determine if Formulaid™ can be administered to the individual child.

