## 3.2 Efficacy Variables

### 3.2.1 Primary Efficacy Variable

Primary efficacy variable in this study is occurrence of sight threatening ROP (ROP stage 3 or worse). All randomized infants will be included in the evaluation of the primary variable. Early drop-outs and deaths before evaluated ROP stage 3 or worse will be considered as non-events and will contribute with their follow-up time in the analysis of comparisons between event rates using Poisson regression. A sensitivity analysis will analyse primary efficacy variable applying survival analyses adjusting for death as competing risk and censoring of those infants that have dropped out due to other reasons than death.

In this study ophthalmologic assessment of ROP stage was performed in blinded manner. Retinal examination were performed approximately once weekly starting at four to five weeks of age according to a standardized protocol and to clinical screening praxis. The evaluation of ROP occurred independently from the study and paediatric ophthalmologists were unaware of which infants were participating in the study.

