## 4.6 Efficacy Analyses

### 4.6.1 Primary Efficacy Analysis

The primary analysis in this study is incidence of sight-threatening (severe) ROP, i.e. ROP stage 3 or worse. Due to early deaths and early discontinuations in study the primary analysis will be performed using Poisson regression studying event rates, where deaths and early drop-outs are contributing as non-events with their follow-up time in the study. From this analysis Relative Risks (RR) and 95% CI for comparison between the groups will be presented along with the p-value. The primary analysis will be adjusted for stratification used in the randomization, i.e. adjusted for centre and GA categories as fixed effects, according to the guidelines issued by EMA (*Points to consider on adjustment for baseline covariates*).

The main analysis will be performed on ITT population. The sensitivity analysis will be performed on ITT population comparing cumulative incidence rates adjusted for death as

|                                     |  |                                    |               |
|-------------------------------------|--|------------------------------------|---------------|
| STATISTISKA KONSULTGRUPPEN          |  | Statistical Analysis Plan          |               |
| Protocol:
Mega Donna Mega |  | Protocol No:
MEGADONNAMEGA 16-7 |               |
|                                     |  | Version:
1.0                    | Page 18 of 21 |

competing risk, other drop-outs handled as censored in the survival analysis. Gray's test will be performed for this purpose. Moreover, the effect of the sensitivity analysis will be explained by Hazard Ratios (HR) with 95% CI obtained from Cox proportional hazards models. The primary analysis will also be performed on PP population as robustness analysis.

Graphically, cumulative incidence curves with 95% CI will be presented per treatment group.

The analysis will be considered confirmed if the p-value <0.05.

The impact of IP on primary variable will also be evaluated descriptively by centre and by GA categories, used in stratification of the randomization.

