### 1. Definition of Safety population

**Original definition:** All enrolled subjects who received at least one dose of randomized investigational product will be included in the safety population.

**Extended definition to be used in the study report:** All randomized infants will be included in the safety population, since all infants are treated according to regular clinical practice, both those randomized to Formulaid and those randomized to not receive Formulaid.

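### The SAP's ITT population is a modified ITT set with an undefined treated condition, and it contradicts the SAP's statement that every randomised infant is evaluated for the primary variable

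*Combined protocol and SAP*

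**What the plan says.** SAP 2.1.1 sets three conditions for the ITT population, namely randomised, correctly included and treated: "All randomized subjects, being correctly included according to the inclusion/exclusion criteria, and have been treated will be included in the Intention-To-Treat (ITT) population". It adds: "The final definition of patients included in the ITT population will be made at the clean file meeting prior to database lock", and asks that exclusions be described in the clean file protocol.

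SAP 4.6.1 then says of the primary endpoint: "The main analysis will be performed on ITT population". SAP 4.6.2 uses the same set for the main secondary analyses. SAP 3.2.1, however, says: "All randomized infants will be included in the evaluation of the primary variable".

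On who knows the allocation, protocol section 4 says: "The treating nurse/doctor will receive the randomization on-line", and "The examiners (ophthalmologists, radiologists and psychologists) will be blinded for fatty acid treatment regime". The control arm has no matching product. Protocol 6.2 says: "A preterm child that is randomized to conventional treatment receives Clinoleic", given as in regular practice.

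A later note to the SAP widens the safety population to all randomised infants, "since all infants are treated according to regular clinical practice, both those randomized to Formulaid and those randomized to not receive Formulaid". Neither that note nor Note-to-SAP 1 touches the ITT definition.

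**The concern.** An ITT analysis keeps the groups that randomisation formed. Here membership depends on something that happens after randomisation (being treated) and on eligibility judged late. The label ITT hides both conditions.

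If treated means having received the supplement, the condition bears on one arm only, and failing it may be linked to how ill the infant is and to choices made by staff who know the allocation. Blinding the eye examiners protects the ROP grading. It does not protect the decision on who is in the set, and no blinding of the clean file meeting is stated.

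All five confirmatory analyses in SAP 4.1 are affected, because their main analyses run on this set. Since the safety population was widened, it can also be larger than the set called ITT.

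**Working it through.** **1. The two rules side by side.** SAP 3.2.1 puts all randomised infants into the primary evaluation. SAP 4.6.1 runs the primary analysis on ITT, and SAP 2.1.1 makes ITT a subset. Both hold only if no randomised infant is untreated or wrongly included. SAP 4.2 plans to report the numbers randomised and treated, so the authors allow that the two may differ.

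**2. Who can fail the treated condition.** There are two readings.
- *Received the supplement.* SAP 1.3 uses the word as the label of the supplement arm. Only that arm can fail. The route is foreseeable: protocol 6.2 anticipates infants who cannot have a first dose within 24 hours, and leaves administration to the responsible clinician.
- *Received regular care.* This is the safety note's reading. Few or no infants fail, in either arm.

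SAP 2.1.1 does not choose between them.

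**3. Who can fail the eligibility condition.** Either arm. Several exclusion criteria in protocol 5.3 rest on the investigator's opinion.

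**4. The plan's own figure.** Protocol 11.1 gives 80 per arm for any ROP, 42% against 22%, alpha 5%, power 80%. With unpooled variance and a two-sided test: (1.96 + 0.842)² × (0.42×0.58 + 0.22×0.78) / 0.20² = 7.85 × 0.4152 / 0.04 = 81.5, within 2 of the stated 80. This figure is not in dispute.

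**5. Very early deaths.** SAP 3.2.1 counts a death before stage 3 as a non-event that contributes its follow-up time. Assume 89 survivors (105 × 0.85) followed for 98 days, and 6 deaths at 2 days. The survivors give 89 × 98 = 8,722 infant-days and the 6 deaths give 12, about 0.14%. Dropping them removes no events and raises the supplement arm's event rate by about 0.14%. The same holds for the main BPD analysis, where deaths are also non-events.

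**6. Other infants.** The documents give no number for undosed infants and no event rate for stage 3 or worse, so this is an assumption grid. Take no true effect, 105 per arm, overall risk p, and k infants with event risk q removed from the supplement arm only. On simple proportions, apparent RR = [(105p − kq)/(105 − k)] / p.

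| p | k | all k would have the event (q = 1) | average risk (q = p) | none would (q = 0) |
|---|---|---|---|---|
| 22% (assumed) | 5 | 0.823 | 1.000 | 1.050 |
| 22% (assumed) | 10 | 0.627 | 1.000 | 1.105 |
| 42% (any-ROP rate) | 5 | 0.931 | 1.000 | 1.050 |
| 42% (any-ROP rate) | 10 | 0.855 | 1.000 | 1.105 |

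For example, (23.1 − 5)/100 = 0.181, and 0.181/0.22 = 0.823. At the extremes q = 1 and q = 0 with k = 5, a two-sided 5% test by the normal approximation has a type I error of about 10.6% and 5.4% at p = 22%, and 7.1% and 6.1% at p = 42%.

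**7. BPD sensitivity analysis.** SAP 3.2.2 counts deaths as endpoints here. With 16 of 105 deaths (15.2%), dropping 4 gives 12/101 = 11.9%, a ratio of 0.78 on the death component alone. If c infants have BPD or death, the ratio is (1 − 4/c) × 105/101. This moves towards 1 as c rises above 16, so 0.78 is the extreme for four removed deaths.

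**8. Power.** For 42% against 22% with pooled variance at 105 per arm: (0.20 − 1.96 × 0.0644)/0.0629 = 1.17, a power of 88.0%. With 100 in the supplement arm it is 87.1%. The issue is bias, not power.

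**The case against.** The strongest reply has four parts.

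- *The safety note shows what treated means.* On that reading almost nobody is lost. This is possible, but the note is confined to the safety population, whose earlier rule in SAP 2.1.3 was at least one dose of randomised product. The sponsor amended that rule and left ITT alone.
- *Few infants will go undosed.* Randomisation follows parental consent (protocol section 4), so deaths before consent are never randomised. The supplement is meant to be given even when feeds are not tolerated (protocol section 4 and Appendix 3). This stands and keeps the likely number small, though clinician discretion remains.
- *Exclusions are fixed before database lock and documented.* This is true. It gives transparency, but it does not prevent selection.
- *Early deaths do not matter.* For the primary and main BPD analyses this stands, as step 5 shows.

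A reader might infer more: that the definition strips the sickest infants from the supplement arm alone and so favours the supplement on every confirmatory endpoint. The documents do not support that. The eligibility condition acts on both arms, and the treated condition is one-sided only on one of two readings. Early deaths are non-events in the ROP and BPD rate models. AA and DHA are modelled as change from birth without imputation, so an infant who dies before dosing has little or nothing to contribute. Missing IVH counts as a non-event in the main analysis. A shift in arm mortality would not show such a bias either, because mortality is not one of the five confirmatory variables.

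**Conclusion.** The point holds as a defect of definition. The set called ITT is a modified ITT set, its treated condition is undefined, its membership is left to the clean file meeting, and it conflicts with SAP 3.2.1 on who is in the primary analysis.

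The size of any bias cannot be known from the documents, and its direction is open. Results could shift if undosed infants survive and differ in ROP or BPD risk, if infants with a recorded IVH are dropped, or if deaths are dropped from the BPD analysis that counts them as endpoints. With 5 of 105 supplement infants removed, a 22% event rate and no true effect, the apparent relative risk lies between 0.82 and 1.05. It is 1.00 if the removed infants carry average risk. The count of 5, the 22% rate and one-sided removal are assumptions, and simple proportions stand in for the planned Poisson model.

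**What to change.** In SAP 2.1.1, define ITT as all randomised infants, analysed in the arm assigned, whatever they received and whether or not an eligibility error is found later. This brings it into line with SAP 3.2.1, so that 4.6.1 and 4.6.2 refer to the same infants. Remove the clean-file decision over ITT membership, except where permission to use the data is withdrawn.

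If an analysis of treated or correctly included infants is wanted, define treated, label the set modified ITT, report it as a sensitivity analysis, and list exclusions by arm and reason. Leave the per-protocol criteria as they stand (final ROP stage available, and compliance of at least 70% as added by the later note).

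The cost is SAP wording. No data beyond those already planned are needed, and keeping every infant does not reduce power.
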